### Health service utilization

Singapore Stroke Study Health Service Utilization Form will be used to perform cost-effectiveness analysis in both tele-rehabilitation and usual care. This form is chosen because it has been contextualized to the local Singaporean context. It comprises of 11-items and for each item, utilisation of a particular service is asked. If the answer is “Yes”, the duration and the expenditure of its usage will be asked. Quality-of-life data based on EQ-5D instrument will be combined with resource utilization and cost data to develop incremental cost-effectiveness ratios that will allow investigators to evaluate the cost-effectiveness of tele-rehabilitation compared to usual care [28].

### Caregiver burden

The Zarit Burden Interview (ZBI), which provides a comprehensive assessment of caregiver burden, has been validated in many culturally and ethnically different populations. In this study, the 12-item version of the ZBI will be used with response options ranging from never =1 to nearly always = 5 [29]. The total score will be calculated to determine the burden levels; the higher the score, the greater the burden. The ZBI demonstrates good validity and reliability in measuring the burden of caregivers in Singapore [29] with duration of caregiving and financial problems correlating with greater caregiver burden.

### Research data management and security

All patient information to and from the server will be encrypted via Hypertext Transfer Protocol Secure (HTTPS) which ensures no external parties are able to view it during transfer, a protocol similar to those used by online banking systems. Data access from server is also authenticated by a passphrase which is supplied from the therapist application, ensuring only the patient’s therapist will be able to request and review patient data. Regarding security on the server side, we will be using the Apache server running on a Unix-based operating system and have taken recommended measures to minimise vulnerabilities from hacking.

Only an administrator (in this study, this is the Study Coordinator) will be able to view all patients (both groups) and therapists (intervention group only) data, and update the system in an event of data entry error. The administrator will have privileges to add patients & therapists to the database, pair patients to therapists as well as to update and view all patient data. The independent assessor (blinded evaluator) will be able to input outcome data into the system for both groups at 3 month and 6 month. However, independent assessor will not have access to any participant information other than the latter’s initials and unique study number. The biostatistician will only have read-only access to all the patients’ data for research purposes. However, the biostatistician will not be able to manipulate or distort the data. The biostatistician can also download data for research purposes in the form of an Excel file. All these measures have been put in place to ensure that there is no leakage of patients’ information and only authorized individuals have full access to the secured data.

### Statistical analysis

#### Sample size

Chumbler et al’s paper had similar tele-rehabilitation intervention at 0, 3 and 6 months, and the same primary outcome measure, the Difficulty dimension of the Disability component of the Jette LLFDI [12]. Even though the mean score derived from the results in Chumbler et al’s paper was 11 [12], a mean score of 8 was used in this study due to different geographical and socio-cultural context; Chumbler et al’s study was done in the United States whereas this study was done in Singapore, where rehabilitation is less well-accepted. Hence, based on a two-sided test of 5 % and a power of 90 %, and assuming a difference in mean scores of 8 and a standard deviation of 16, and a correlation of 0.6, a total sample size of around 86 (intervention = 43, controls = 43) was calculated to be adequate. Accounting for 14 % attrition rate, the minimum sample size was determined to be 100 (intervention = 50, controls = 50). It is planned that 100 participants will be recruited within 2 years, after which an additional 6 months is needed for follow-up.

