## Discussion

The STARS Study is a multi-site randomized controlled trial designed to determine the impact of video-conferencing and the use of wearable monitoring devices compared to usual care on the functional recovery of stroke survivors. Stroke results in disabling limitations for patients and supervised rehabilitation can improve functional recovery, but only a minority is undergoing supervised rehabilitation one month after discharge into the community [1]. This trial will make several contributions to the practice of rehabilitation after stroke. Firstly, it will test the practicability of a tele-technology aided rehabilitation intervention on a sufficient number of participants to provide a reasonable basis for confident inference to clinical practice. Secondly, this trial will also test the secondary outcomes of tele-rehabilitation in terms of gait speed, contact time with a therapist, balance, self-reported health-related quality of life, health service utilization and caregiver burden in comparison to usual care. Next, the trial will examine if any greater functional improvement in the intervention group is due to better adherence to supervised exercise or independent of better adherence to supervised exercise. Lastly, the tele-technology aided rehabilitation intervention will be tested against usual care to provide an economic evaluation that incorporates resource utilization and patients’ valuation of their quality of life over the trial period, helping to determine the cost-effectiveness of tele-rehabilitation. Previous studies of the cost of stroke in Singapore estimate only total hospital costs for patients [30] and no published studies has examined the cost-effectiveness of tele-rehabilitation over usual care. Optimal usage of technologies in nationwide post-stroke rehabilitation remains a subject of discussion amongst healthcare decision makers and one of the most paramount problems that stops them from implementing it is due to cost. The trial will provide a start in the process of weighing the clinical and economic costs and benefits.

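### The sample-size inputs do not give 43 per arm at 90% power: the three-month endpoint needs about 55 to 86 per arm, and 43 gives about 63% to 82% power

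*Protocol article*

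**What the plan says.** All the inputs are in the Sample size section of the protocol article. The calculation is "based on a two-sided test of 5 % and a power of 90"%, assuming "a difference in mean scores of 8 and a standard deviation of 16, and a correlation of 0.6, a total sample size" of about 86. The result is stated as "a total sample size of around 86 (intervention = 43, controls = 43) was calculated to be adequate". After 14% attrition, "the minimum sample size was determined to be 100", with 50 in each arm.

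The section names no formula. It does not say which two measurements correlate at 0.6, or whether 16 is the SD of the score or of its change.

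Other sections fix the rest of the design. The Abstract and Background place the primary LLFDI comparison at three months, and the Background uses the six-month visit to see whether any gain lasts. Randomisation method sets equal allocation. Analysis for outcome measures names a two-sample t-test, ANCOVA and adjusted regression. It describes no model that pools the three- and six-month values.

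**The concern.** Difference, SD, significance level and power together determine the size of a two-group comparison, apart from the gain from using baseline. A difference of half an SD at 90% power needs about 85 per arm without baseline. For 43 to be right, the correlation would have to halve that number, and 0.6 is too weak to do so in an analysis of one follow-up.

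The stated power governs how a negative result is read. The section lowers the target difference from 11 to 8 because rehabilitation is less well accepted locally, so the ability to detect 8 is the point of the calculation. The Discussion then describes the trial as run "on a sufficient number of participants to provide a reasonable basis for confident inference to clinical practice". If real power is well below 90%, a null finding would be taken as good evidence of no benefit when an 8-point effect could easily have been missed.

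**Working it through.** **Inputs** (Sample size section): two-sided α = 0.05, power 90%, difference 8, SD 16, correlation r = 0.6, 43 per arm evaluable, 14% attrition. Allocation is 1:1, with one primary follow-up at three months.

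**The plan's own figures.** The attrition step reproduces: 86/0.86 = 100. The 43 per arm does not, as follows.

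**Formula.** Normal approximation, per arm:

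n = 2 × (1.95996 + 1.28155)² × (16/8)² × f = 2 × 10.507 × 4 × f = 84.06 × f

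Here f is the variance factor for how the correlation is used:

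- no baseline: f = 1
- change score: f = 2(1 − r) = 0.80
- ANCOVA on baseline: f = 1 − r² = 0.64

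Sizes by noncentral t, and power by noncentral t at 43 and 50 per arm:

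| Analysis of the 3-month outcome | n per arm, normal (unrounded) | n per arm, t | Power at 43 | Power at 50 (no attrition) |
|---|---|---|---|---|
| ANCOVA on baseline | 53.8 | 55 | 81.7% | 87.2% |
| Change score | 67.2 | 69 | 72.7% | 79.0% |
| 3-month scores only | 84.06 | 86 | 63.0% | 69.7% |

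No row gives 43. The smallest requirement, 2 × 55 = 110 in total, exceeds 86 by 24/86 = 28%, which the word 'around' does not cover.

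**Detectable difference at 90% power with 43 per arm** (noncentral t): about 9.1 by ANCOVA, 10.1 by change score and 11.3 without baseline. For ANCOVA to reach 90% power for 8 points at 43 per arm, r would have to be about 0.71.

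**Enrolment needed to keep 90% power for 8 points with 14% attrition:** 110/0.86 = 128 by ANCOVA; 172/0.86 = 200 without baseline.

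**Other readings tried:**

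- If 16 is the SD of the change, the normal-approximation size becomes 68 per arm (ANCOVA) or 85 (change score), so the gap widens.
- ANCOVA with one-sided 5% gives 44, but the text says two-sided.
- ANCOVA with r = 0.7 gives 43 by the normal approximation, but the text says 0.6.
- Applying both the change-score and the ANCOVA factor gives 84.06 × 0.80 × 0.64 = 43.04, which counts the correlation twice.
- The one-sample formula gives 10.507 × 4 = 42.03, rounded up to 43, but it omits the factor of 2 for two groups. The unadjusted t-test size is 86 per arm, the number the article gives as its total. A lost factor of 2 would fit both figures, but the document cannot settle where they came from.
- ANCOVA on the mean of the three- and six-month scores, all correlations 0.6, has f = (1 + 0.6)/2 − 0.36 = 0.44. It needs 37 per arm (38 by t), and 43 per arm would give about 93% power.

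**The case against.** The strongest defence is the last reading. The section introduces its calculation by citing a study assessed at 0, 3 and 6 months, the same schedule as this trial. If the authors meant ANCOVA on the mean of both follow-ups, 43 per arm is more than enough, and a size above the requirement still delivers the stated power. This shows that the claim of a shortfall depends on which endpoint is analysed. It does not rescue the text, because the article fixes the primary comparison at three months, describes no repeated-measures model, and that calculation gives 37 or 38 rather than 43.

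A second point is fair as a qualification. The 86 per arm and 63% power leave out a correlation that the article states. With that correlation used, the range is 55 to 69 per arm and 73% to 82% power, and the risk of missing the effect is 18% to 27%. The no-baseline row stays in the range because a t-test is among the named analyses and the role of the correlation is never stated, but it is the unfavourable end.

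Two smaller points also stand. The Discussion sentence concerns practicability and quotes no power, so it leans on the calculation without repeating the error. And although the LLFDI is not in the baseline table, the outcome is defined as an improvement, which implies a baseline value; a condensed article may simply not list it. That makes the ANCOVA figure the likelier one, but even that figure is not 90%.

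**Conclusion.** The concern holds. For the stated three-month primary outcome, a difference of 8, SD 16 and r = 0.6 at two-sided 5%, 43 per arm gives about 82% power by ANCOVA, 73% by change score and 63% without baseline. The chance of missing the target effect is about 1.8 to 3.7 times the stated 10%. Full retention of 50 per arm would not restore 90% power under any of these analyses.

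This rests on equal allocation, a common SD of 16 for the score, and 0.6 as the correlation between baseline and three months. The last two are readings of an unexplained input. Taking 16 as the SD of change makes matters worse. Only a primary analysis that pools both follow-ups would remove the shortfall, and the article does not plan one. The source of the 43 cannot be established from the document, and the conclusion does not depend on it.

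**What to change.** Keep 100 patients and correct the statement in the Sample size section:

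1. Name the formula, and say which measurements the 0.6 correlates, whether 16 is the SD of the score or of the change, and which primary analysis uses them.
2. If that analysis is ANCOVA on baseline LLFDI, replace the 90% claim with wording such as: '43 evaluable participants per arm give about 82% power to detect a difference of 8 (SD 16) at three months by ANCOVA on baseline LLFDI with a correlation of 0.6; the difference detectable with 90% power is about 9.'
3. If no baseline LLFDI is collected, state about 63% power and a detectable difference of about 11.
4. Read the Discussion's remark on sufficient numbers in the light of the restated power.

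The cost is wording only. No extra patients or visits are needed, but the declared power becomes less favourable. Keeping 90% power for 8 points would instead mean enrolling about 128 (ANCOVA) to 200 (no baseline).

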#### Analysis for outcome measures

Data entered will be checked for accuracy at least twice by at least two independent assessors. To understand the structure of missing data and to reduce bias from uncertainty of missing data, multiple imputations will be performed using the Markov Chain Monte Carlo method. All scale-based measures used in this study will be screened via an internal consistency test (Cronbach’s alpha test) before creating a summative score. Furthermore, rigorous validity tests will be performed in two ways: person-centered tests (latent class analysis) and variable-centered tests (exploratory and confirmatory factor analyses).

For descriptive statistics, independent two-sample *t*-test and Analysis of Covariance (ANCOVA) will be performed on all continuous outcome measures (i.e. Shah-modified BI, ABC Scale, gait speed, two-minute walk test and ZBI) between tele-rehabilitation vs. usual care group if outcomes are normally distributed. Mann–Whitney *U* test will be performed on data with skewed distribution to test differences between treatment groups. Chi-square test will be performed on categorical variables. Confounders are age, gender, ethnicity and marital status. Multiple linear regressions will be used to adjust for differences in confounders between intervention and control groups for continuous outcome variables. Ordered logistic regressions will be used to adjust for differences between intervention and control groups for continuous categorical variables. For these multivariate linear and logistic regressions, we will use survey analysis processes with robust standard errors which accounts for nesting effects within patient data as a result of clustering by different recruitment centers. For all statistical analyses, the level of significance (α) will be taken at 0.05. Analyses will be based on the intention-to-treat approach. We will use STATA version 12 for statistical analysis and significance level is set at P < 0.05.

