### Participant recruitment

Participants will be recruited from the inpatient rehabilitation unit of an acute hospital (i.e. SGH) and an inpatient rehabilitation hospital (i.e. AMKTHKH). Each site is expected to recruit approximately 50 participants (25 intervention and 25 controls).

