### Randomisation method

Randomization will be conducted after baseline assessment. The participants will be randomized into one of the two groups: tele-rehabilitation intervention and usual care based on equal allocation with randomly varying block sizes of four and six. As the study is conducted in two sites, stratified randomisation will be carried out assuming study site as the stratification factor. The randomisation list is generated using the ***ralloc*** package of Stata 11 (StataCorp LP, College Station, TX, USA).

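### Robust standard errors clustered on two recruiting centres leave 1 degree of freedom, so the adjusted regressions lose most of their power

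*Protocol article*

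**What the plan says.** All references are to the protocol article.

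- *Analysis for outcome measures*: continuous outcomes are adjusted by multiple linear regression and ordered categorical outcomes by ordered logistic regression. These models are to rest on "survey analysis processes with robust standard errors which accounts for nesting effects within patient data as a result of clustering by different recruitment centers". The covariates named are age, sex, ethnic group and marital status; centre is not among them. On the test level: "For all statistical analyses, the level of significance (α) will be taken at 0.05".
- *Randomisation method*: "As the study is conducted in two sites, stratified randomisation will be carried out assuming study site as the stratification factor". Participants are the units allocated, "based on equal allocation with randomly varying block sizes of four and six".
- *Participant recruitment*: two hospitals are named, and "Each site is expected to recruit approximately 50 participants", half in each arm.

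The article gives no degrees-of-freedom rule and no small-sample correction for the clustered variance.

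**The concern.** A cluster-robust variance is estimated from the variation between clusters, so its reliability depends on the number of clusters and not on the number of patients. Two clusters give one independent contrast. The number of centres is fixed by design at two, so this cannot improve as recruitment proceeds.

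The choice also does not match the randomisation. Both arms are present in each centre in about equal numbers, so a difference in level between centres cancels out of the treatment comparison. The stratified design calls for site to be a term in the model.

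At stake are the standard errors, intervals and p-values of the covariate-adjusted treatment comparisons. The same section introduces the t-test and ANCOVA under descriptive statistics, so the regressions may be expected to carry much of the inference.

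**Working it through.** The plan gives no figure of its own on this point, so there is none to reproduce.

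**Inputs**
- Clusters G = 2 (*Randomisation method*; *Participant recruitment*).
- Two-sided test at 5% (*Sample size*: "based on a two-sided test of 5 % and a power of 90"%).
- Difference 8, SD 16, correlation 0.6, 86 evaluable patients (*Sample size*). With equal sites and arms, 86 / 2 = 43 per site and 43 per arm.
- Residual SD (assumed range): 16 with no gain from covariates, down to 16 × √(1 − 0.6²) = 12.8 if a baseline score correlated 0.6 with the outcome were in the model.

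**Step 1: degrees of freedom.** Design df = G − 1 = 1. The two-sided 5% critical value of t on 1 df is 12.706; on patient-level df it is about 1.99.

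**Step 2: what the clustered standard error becomes.** Let b1 and b2 be the treatment effects in the two centres. With balanced arms and equal centres, the overall estimate is (b1 + b2)/2. The two centre score sums add to zero, so they are +(b1 − b2)/4 and −(b1 − b2)/4. With the multiplier G/(G − 1) = 2:

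SE² = 2 × 2 × (b1 − b2)²/16 = (b1 − b2)²/4, so SE = |b1 − b2|/2.

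Under normal errors this equals the true standard error times |Z|, with Z standard normal. The test statistic is then exactly t on 1 df under the null, whatever the SD.

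**Step 3: type I error.**
- Reference t(1): 5% by construction (simulated 4.8–5.4%).
- Normal reference: P(|t₁| > 1.96) = 0.300 (simulated 29–31%).

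**Step 4: power for a difference of 8, 43 per arm.** True SE = SD × √(2/43). The noncentrality is 8/SE.

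| Residual SD | True SE | Noncentrality | Power, t(1) | Power, patient-level SE |
|---|---|---|---|---|
| 16 | 3.45 | 2.32 | 14.5% | 63% |
| 12.8 | 2.76 | 2.90 | 18.0% | 82% |

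With 50 per arm, the t(1) power is 15.6% (SD 16) to 19.4% (SD 12.8), against about 70% to 87%. Simulations with residual SD 12.8 and 86 or 100 patients, with and without four covariates and a site term, gave 17–20% on t(1) and 79–88% with patient-level standard errors.

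**Step 5: interval width.** The median of |Z| is 0.6745. The median clustered 95% width is 2 × 12.706 × 0.6745 × SE.
- SD 12.8: 17.14 × 2.76 = 47 points, against 2 × 1.99 × 2.76 = 11.
- SD 16: 17.14 × 3.45 = 59 points, against 2 × 1.99 × 3.45 = 14.

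The ratio is about 4.3 in both cases. The clustered SE itself is erratic: at SD 12.8 its 5th to 95th percentile range is 0.17 to 5.4, around a true 2.76.

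The exact results are for linear regression. In the ordered logistic model the two centre score sums also add to zero, so the single degree of freedom carries over, but the power figures were not computed for it.

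**The case against.** The sentence is loose. It names neither a sampling unit nor a stratum, and site is elsewhere called the stratification factor. A survey set-up with site as stratum and patient as unit would have roughly N − 2 df and none of this problem, and an article may leave such set-up details to a fuller document. Part of this stands: the defect depends on centre being the cluster. But the article speaks of clustering by centre, and that is the ordinary reading. If a stratum was meant, the sentence still needs changing.

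Three stronger readings are tempting, and the document does not support them.

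- *That the plan carries a 30% false-positive rate.* The plan names survey procedures, which refer the statistic to t on the design df, and there the test holds its level. The 30% needs a normal (or patient-level) reference, which the article does not mention. The planned tests are weak rather than invalid.
- *That almost all power is lost, from 82% to 18%.* Some 15–18% remains, so most of the power is lost. The 82% assumes adjustment for a baseline score, which is not among the listed covariates; without it the comparator is 63%.
- *That every treatment comparison is compromised.* The clause covers only the adjusted linear and logistic regressions. The t-test, ANCOVA, Mann–Whitney and chi-square comparisons are unaffected. The article does not say which analysis is primary, and its list of continuous outcomes does not name the LLFDI.

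**Conclusion.** Wrong as written. The stated variance method does not fit the stated design: centre is a two-level stratum of an individually randomised trial, and clustering on it leaves 1 design degree of freedom.

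On the survey t(1) reference, the adjusted linear regressions keep type I error near 5%. Their power for an 8-point difference falls from 63–82% to about 15–18% at 43 patients per site, and the median interval is about four times too wide. A cluster-robust fit with a normal reference would instead give a type I error of about 30%.

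The single degree of freedom and the 30% follow from having two clusters and do not depend on the assumed SD. The power figures rest on normal errors, equal centres, balanced arms and the assumed residual SD range of 12.8 to 16. The conclusion is confined to the adjusted regressions.

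**What to change.** Delete the clause on clustering by recruitment centre. Fit each adjusted linear or ordered logistic model with treatment and site as a fixed effect, because site is the stratification factor, and use model-based or heteroscedasticity-robust standard errors at patient level. In simulation of the linear model, patient-level standard errors gave a type I error of 4.4–5.0%.

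If the survey commands are to be kept, declare site as the stratum and the patient as the sampling unit, and say so in the text.

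Either change is one sentence and needs no new data or patients. It should be made before the unblinded analysis, so that the choice of standard error is not made with the results in view.
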